# A study protocol for a cluster randomized controlled trial to test the applicability of the South African diabetes prevention program in the Eastern Cape Province of South Africa

**DOI:** 10.1186/s12889-022-14884-1

**Published:** 2023-01-31

**Keywords:** Diabetes prevention, Community-based intervention, Behavioural change, Lifestyle intervention, Translational research, South Africa

## Abstract

**Background:**

Convincing evidence supports the effectiveness of lifestyle interventions in preventing the occurrence of diabetes in high-income countries, however little is known about appropriate interventions for use in African countries, where there are higher relative increases in diabetes prevalence. The South African Diabetes Prevention Programme (SA-DPP) was initiated with the aim of preventing or delaying the occurrence of diabetes among South Africans (SAs), through interventions, targeting lifestyle changes related to diet and physical activity. The purpose of the current project is to implement and evaluate the suitability and applicability of the SA-DPP developed and tailored in urban populations in the Western Cape Province, in peri-urban populations in the Eastern Cape Province of SA.

**Methods:**

The SA-DPP, which is an cluster randomized control trial, will be implemented in adults aged 30–65 years residing in the OR Tambo district, Eastern Cape, SA. Participants will be recruited using self-selected sampling techniques and 24 clusters across peri-urban communities will be randomly allocated to participate in the lifestyle intervention, facilitated by non-professional health workers (NPHW). The diabetes risk screening will follow a two-staged approach, including the community-based screening, using the African diabetes risk score (ADRS), followed by a clinic-based risk status assessment by an oral glucose tolerance test (OGTT) to exclude unknown diabetes. The lifestyle-change objectives of the current programme relate to, 1) < 30% of total energy intake from fat; 2) < 10% of total energy intake from saturated fat; 3) > 15 g of fibre/1000 kcal; 4) > 4 h/week moderate level of physical activity; and 5) > 2% body mass index (BMI) reduction.

**Discussion:**

The SA-DPP could represent a successful model for the prevention of diabetes and potentially other lifestyle-related diseases in SA and other countries in the region that are confronted with similar challenges.

**Trial registration:**

PACTR202205591282906.

**Supplementary Information:**

The online version contains supplementary material available at 10.1186/s12889-022-14884-1.

## Background

The global prevalence of diabetes mellitus has substantially increased over the past few decades [1]. According to the latest global estimates, 537 million (10%) of adults are currently living with diabetes, with Africa predicted to experience the largest relative increase of new cases over the next 24 years [1]. Indeed, it is projected that the population with diabetes in Africa, which is mainly driven by type 2 diabetes mellitus (T2DM) [2], will increase by 129% from 24 million to 55 million by 2045 [1]. South Africa has the highest age-adjusted prevalence of diabetes in adults aged 20–79 years in the African region [2], with the greatest burden experienced in socio-economically disadvantaged communities. It is further estimated that at least a similar proportion of adult South Africans without diabetes, are at high risk of developing the disease in future.

Community-based risk screening and prevention strategies, like lifestyle interventions, are frequently advocated to reduce the growing global burden of T2DM. However, despite the convincing evidence from high-income countries on the effectiveness of lifestyle interventions in preventing diabetes among high-risk individuals [3, 4], little is known about implementing these interventions in real-life settings in Africa. The South African Diabetes Prevention Programme (SA-DPP) was initiated by the Non-Communicable Diseases Research Unit (NCDRU) of the South African MRC (SAMRC) to generate such evidence for South Africa (SA) that could inform similar initiatives in other countries in the African region. The SA-DPP is an intervention, which was developed and tailored in urban populations, comprising three components, namely, [1] home/community-based screening by non-professional health workers (NPHW) to detect those at high risk of developing T2DM using a non-laboratory-based diabetes risk score (the African Diabetes Risk Score, ADRS) [2, 5]; delivery by NPHW of group-based task-oriented and culturally tailored socio-behavioural counselling targeting the lifestyle change objectives achieved in the Finnish Diabetes Prevention Study (DPS) [i.e. A) < 30% of total energy intake from fat; B) < 10% of total energy intake from saturated fat; C) > 15 g of fibre/1000 kcal; D) > 4 h/week moderate intensity physical activity; and E) > 5% weight reduction [3, 6]; structured cell-phone messaging to enhance program adherence and retention. While the SA-DPP is adapted from programmes previously shown to be effective in Finland [6], Australia [7], and India [8], it has undergone extensive adaptation to be culturally appropriate for South Africa (see Additional file 1 for intervention descriptions). For the SA-DPP to be relevant to the greater South African population it is important to test the intervention in other South African communities. The OR Tambo District Municipality in the Eastern Cape Province, South Africa, was selected because of the continuously increasing proportion of newly diagnosed T2DM cases observed [9].

The current protocol is for a project to implement and evaluate in peri-urban populations in the Eastern Cape Province, the suitability, applicability, appropriateness, and success of the SA-DPP developed and tailored in urban populations in the Western Cape Province of South Africa.

## Methods

### Study objectives

The primary objective of this study is to determine the weight change of participants receiving the lifestyle intervention at the end of a 12-month period. We are testing the hypothesis that the SA-DPP lifestyle intervention can prevent or delay the occurrence of diabetes among high-risk South Africans, by demonstrating that T2DM incidence during follow-up is lower among those who receive the intervention compared to those in the control group. The resources required to demonstrate such an effect, which include large sample sizes, long duration of follow-up and costly biochemical investigations, are far beyond what can be achieved in most settings. However, literature shows that change in body adiposity, which is apparent within few weeks-to-months, is a very strong predictor of future change in diabetes incidence. Accordingly, the outcome measure for this objective is to evaluate change in weight and consequent body mass index (BMI).

Our secondary objectives are to determine, 1) the level of attainment of lifestyle intervention objectives (including dietary, physical activity); 2) mean differences in fasting blood glucose, HbA1c, BMI; 3) changes in blood pressure, lipid profile and waist circumference; 4) change in insulin sensitivity; 5) change in diabetes risk score and 6) incident diabetes.

Our tertiary objectives include, 1) descriptive analysis of the process involved in the intervention; 2) retrieving qualitative feedback from intervention participants; 3) conducting analysis of impact on lifestyle (i.e., quality of life, dietary and physical activity behavioural changes) and 4) evaluating the economic impact of the intervention.

### Study design

This study is a fixed matched unblinded randomized cohort design with 12 clusters per arm. To reduce between-unit (between-cluster) variability in the estimation of the intervention effect, reduce the standard error and increasing power and precision [8, 10], clusters will be organized into pairs, with one cluster within each pair assigned to a study arm. Twenty-four (24) clusters (12 intervention and 12 control) across peri-urban communities in OR Tambo district in the Eastern Cape, South Africa will be randomly allocated to participate in a lifestyle intervention facilitated by teams of NPHW.

### Site selection and sampling frame

The OR Tambo District Municipality is located on the coastline at the east end of the Eastern Cape Province, South Africa. The district consists of five local municipalities, namely King Sabata Dalindyebo, Nyandeni, Mhlontlo, Port St Johns and Ingquza Hill and it is one of the four Integrated Sustainable Rural Development Programme (ISRDP) nodes in the Eastern Cape Province. The district has a population of 1,457,384 with a population growth of 1.47% annually. According to the most recent statistics, 99.04% of the population is black, with 25.35% (*n* = 345,944) between the age of 30 and 65 years.

### Study population

The study population will comprise South Africans aged 30–65 years, permanently residing in the OR Tambo district. The justification for the age bracket is motivated by, 1) the fact that available tools for T2DM risk screening at the community level have been designed and validated for use in this age group; 2) most people at risk of T2DM are likely to be found in this group; and 3) intervention in a more elderly population may require programmes that are specific to that age range [11]. Our pilot project in Cape Town, South Africa, has also indicated that among people at high risk of diabetes, based on a risk score, and further go on the be at high risk, by oral glucose tolerance test, are typically aged older than 30 years [12]. Further criteria for inclusion into our study includes being fluent in Xhosa or other dominant languages in the area (Afrikaans, English), being able to give informed consent and willing to participate in a lifestyle intervention trial. We will exclude individuals with known or screen-detected diabetes, active tuberculosis, major illness, or those that are bedridden. Individuals with severe mental illness or substance abuse will also be excluded as these conditions may likely interfere with participation and/or ability to consent. Finally, we will exclude individuals using medication that can affect glucose tolerance and women that are currently pregnant or planning for a pregnancy.

### Sample size calculation

To detect a minimum clinically relevant mean weight difference of 2 kg (±5.8, standard deviation) between intervention and control clusters [13], assuming an 80% power, a two-sided alpha of 5% and an intra-cluster correlation coefficient (ICC) of 0.02 [14], and accounting for a 20% drop-out during follow-up, we require 12 clusters of 20 participants per study arm; equalling 24 clusters and 480 participants. Using the same assumptions as above, Table 1 below presents the total number of clusters and participants required for various cluster sizes. For a population with an average starting weight of 80 kg, a mean weight difference of 2 kg correspond to 2.5% change, with the study being adequately powered to detect even larger effect sizes, such as those achieved in the Finnish DPS. A 1 kg change in weight at 1 year is associated with approximately 16% reduction in T2DM incidence at 3 years [15]. The sample size was calculated using the CRTSize package version 1.0 (R statistical software; The R Foundation for Statistical Computing Platform).

**Table 1 Tab1:** Total number of clusters and participants required for various cluster sizes

Number per cluster	5	6	8	10	12	15	16	18	20
**Number per cluster accounting for 20% drop-out**	7	8	10	13	15	19	20	23	25
**Total clusters**	60	52	40	34	30	26	**24**	22	22
**Total sample**	420	416	400	442	450	494	**480**	506	550

### Recruitment processes

Community-based screening (Fig. 1) will be conducted in the O.R. Tambo district (Additional file 2: Map of OR Tambo district). The district consists of nine cities, namely: Mthatha (previously Umtata), Tsolo, Port St Johns, Qumbu, Flagstaff, Libode, Lusikisiki, Mqanduli, Ngqeleni (Additional file 2: Map of OR Tambo). Six clusters (suburbs/townships) will be selected from the largest town (Mthatha), that has a population size of approximately 96,111 people. Then, four clusters from Tsolo (7794 people) and two clusters each will be selected from the seven smaller towns, where population density varies between approximately 2629 to 6500 people. Following community entry and buy-in, information flyers will be distributed to community members inviting them to attend various screening sites at a central community venue (clinic/community centre). Eligible community members deemed at high risk of developing diabetes, using the African Diabetes Risk Score (ADRS) [5] will be invited for further baseline evaluation and to participate in the intervention study. The ADRS [5] is based on three variables (age, waist circumference and hypertension status), and has been shown to have a good predictive accuracy (c-statistic = 0.82 [95%CI: 076–0.87]) during external validation in Black South Africans [5]. Baseline assessments will occur at the nearest clinic or community health care facility or in a mobile clinic if the area is too remote.

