**Fig. 1 Fig1:**
[figure not shown]
Community screening

Twenty-five participants per cluster will be recruited (oversampling to account for 13–20% expected to have undiagnosed diabetes) to undergo the full baseline evaluation, including oral glucose tolerance tests (OGTTs) and glycated haemoglobin (HbA1c). Participants classified as having diabetes at this point will be excluded from the study and suitably referred.

Consenting eligible participants that fulfil the inclusion criteria will be required to complete a brief questionnaire and examination to complete the diabetes risk evaluation. Those identified as high risk via the ADRS will be assigned to commence with the intervention at the randomly pre-defined time-point for their cluster. Clusters will be created according to residential areas of participants.

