### Randomisation

Matched pairing will be done for clusters according to the information available for the population, including for example, size of the cluster, whether they are peri-urban or rural and for factors that are likely to be associated to the outcome. Members of the paired clusters will then be randomized to an intervention or control arm. The differences between the paired clusters after the intervention are then most likely due to the intervention.

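### The recruitment text leaves open whether volunteers are enrolled before or after their cluster is randomised, so recruitment in this unblinded trial could differ by arm

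*Protocol article*

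**What the plan says.** Four features of the protocol article bear on this point.

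- **Who is recruited.** The abstract (Methods) says "Participants will be recruited using self-selected sampling techniques". Under Recruitment processes, "information flyers will be distributed to community members inviting them to attend various screening sites". Eligibility under Study population includes willingness to join a lifestyle trial.
- **Blinding and arms.** Under Study design: "This study is a fixed matched unblinded randomized cohort design with 12 clusters per arm". Under Control groups, control participants receive a healthy-living guide and are offered the intervention when the study ends.
- **What a cluster is.** Recruitment processes chooses clusters by place: "Six clusters (suburbs/townships) will be selected from the largest town (Mthatha"), then four in Tsolo and two in each of seven smaller towns. Later the same section says: "Clusters will be created according to residential areas of participants".
- **When allocation happens.** Under Randomisation, "Matched pairing will be done for clusters according to the information available for the population", and the members of each pair are then randomised. The section does not place this step before or after individual recruitment. Recruitment processes says that those found to be at high risk "will be assigned to commence with the intervention at the randomly pre-defined time-point for their cluster".

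The Randomisation section goes on to attribute differences between paired clusters after the intervention mainly to the intervention.

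**The concern.** Randomising clusters balances areas. It does not balance people who volunteer once the allocation of their area is known. If recruiters or residents know the arm, people drawn to a group programme may come forward in one arm and a different mix in the other. Motivation of that kind plausibly predicts 12-month weight change, the primary outcome.

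Such a difference does not shrink as the sample grows, and covariate adjustment deals only with the part that is measured. The attribution made under Randomisation depends on avoiding it. The consequences go beyond the trial: the Data Availability section ties a significant effect on outcomes such as body weight to a report asking the Department of Health to take over the programme.

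**Working it through.** **Step 1: is the cluster defined before or after recruitment?** The selection by town gives 6 + 4 + 7 × 2 = 24 clusters, the full number in the design, and the section describes it ahead of the flyers. Pairing uses population information, so neither pairing nor randomisation needs an enrolled participant. On this reading, clusters are fixed areas and can be randomised before anyone is screened. The sentence that forms clusters from participants' residence says the reverse: recruitment first, clusters afterwards. A set of areas chosen and paired in advance cannot also be built from whoever enrols, unless that sentence means only that people are assigned to the fixed area in which they live.

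**Step 2: does the random assignment exist when a person is identified?** The start time-point is described as randomly set in advance for the cluster. In a two-arm parallel design where controls are offered the programme only at study end, a cluster's start time in effect reveals its arm. That is an inference, because the word pre-defined attaches to the time-point and not to the arm. Nothing in the article says that enrolment closes before allocation or that recruiters are kept unaware of it.

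**Step 3: the plan's own sample size.** Inputs from Sample size calculation: difference 2 kg, SD 5.8 kg, two-sided alpha 5%, power 80%, ICC 0.02, 16 analysed per cluster (20 after 20% drop-out).

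- Per arm without clustering: 2 × (5.8 × (1.960 + 0.842)/2)² = 132.0
- Design effect: 1 + (16 − 1) × 0.02 = 1.30
- Clusters per arm, normal approximation: 132.0 × 1.30/16 = 10.73
- Clusters per arm with t quantiles on 22 degrees of freedom: 11.75, so 12 per arm and 24 in total
- Recruits: 16/0.8 = 20 per cluster; 24 × 20 = 480

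The stated 24 clusters and 480 participants are reproduced. The sample size is not at issue.

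**Step 4: what a recruitment difference would do.** The standard error of the arm difference is 5.8 × √(2 × 1.30/(12 × 16)) = 0.675 kg. With no true effect and a recruitment-induced difference b, the test statistic is noncentral t with noncentrality b/0.675. The values of b are assumptions; the article gives none.

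| Assumed b (kg) | Share of 2 kg target | b/SE | Two-sided error, 22 df | Two-sided error, 11 df |
|---|---|---|---|---|
| 0 | 0% | 0 | 5.0% | 5.0% |
| 0.25 | 12.5% | 0.37 | 6.5% | 6.3% |
| 0.5 | 25% | 0.74 | 10.9% | 10.4% |
| 1.0 | 50% | 1.48 | 29.4% | 27.3% |

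The last column uses the degrees of freedom of a paired analysis (12 pairs) with the same standard error. It does not credit any precision gained from matching.

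**The case against.** The strongest reply is that the unsafe order is never stated. A reader might infer that people in a known intervention area come for a programme and people in a known control area come for a leaflet. The article does not support that. It describes no arm-specific flyer, only invitations to screening sites. Eligibility is the same in both arms, and controls are promised the programme later. Calling the trial unblinded does not say who knows the allocation before consent. Read literally, the time-point sentence has every high-risk person start the intervention, which does not fit a parallel design, so its wording cannot carry much weight alone. The residence sentence and the statement under Control groups that standard care follows screening are both compatible with the safe order. The screening figure and the timeline table are not reproduced here, and an article may leave concealment details to the full protocol.

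Most of this stands, and it is why the point is a risk and not a demonstrated bias. It does not dispose of the point. The objection is not to silence on concealment. The article makes two statements that point in opposite directions, and one of them suggests that the assignment comes first.

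It would also be too strong to say that motivation goes unmeasured. Table 2 collects exercise self-efficacy and barriers to physical activity, and the analysis section plans pre-specified individual covariates. The process evaluation compares eligible people who did and did not proceed, and exclusions are to be reported at each step. The common risk score and the target of 25 recruits per cluster standardise measured risk and numbers. These measures limit or help to reveal a recruitment difference. They do not remove differences in willingness that the scales miss.

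**Conclusion.** The point holds as an inconsistency with a practical consequence. Recruitment processes and Randomisation do not agree on whether clusters are fixed areas or are formed from participants. The time-point sentence reads as if the random assignment precedes identification. With self-selected volunteers and no blinding, the plan as written permits recruitment to differ by arm.

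The size is illustrative: a two-sided error of about 6.5%, 11% or 29% for an assumed difference of 0.25, 0.5 or 1.0 kg. This rests on the plan's SD, ICC and 16 completers per cluster, and on 22 degrees of freedom. It shows what a bias of that size would do, not that this trial has one. Nor does the article show that the attribution under Randomisation is false; that attribution is conditional on recruitment being comparable in the two arms.

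**What to change.** Define the 24 clusters by area boundary and pair them on population data. In both clusters of a pair, complete the flyers, ADRS screening, consent, OGTT and baseline measurements and close both lists. Only then draw and reveal that pair's allocation. Replace the two sentences in Recruitment processes (the randomly set time-point and the creation of clusters from residence) with this sequence, and state it under Randomisation too.

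If recruitment is already meant to precede allocation, correcting the text is enough. If allocation cannot wait, keep the recruiting staff unaware of it and report recruitment and refusal by arm.

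The change needs no extra participants or visits. Its cost is that the first cluster of a pair waits for the second. Because follow-up runs 12 months from baseline within a 24-month project, a long wait would shorten the time between the start of the intervention and the final measurement. Baseline work in the two clusters of a pair should therefore be scheduled close together.

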**Fig. 1 Fig1:**
[figure not shown]
Community screening

Twenty-five participants per cluster will be recruited (oversampling to account for 13–20% expected to have undiagnosed diabetes) to undergo the full baseline evaluation, including oral glucose tolerance tests (OGTTs) and glycated haemoglobin (HbA1c). Participants classified as having diabetes at this point will be excluded from the study and suitably referred.

Consenting eligible participants that fulfil the inclusion criteria will be required to complete a brief questionnaire and examination to complete the diabetes risk evaluation. Those identified as high risk via the ADRS will be assigned to commence with the intervention at the randomly pre-defined time-point for their cluster. Clusters will be created according to residential areas of participants.

